### Trial design

1.3

The trial design is a 2-arm parallel group Type II hybrid effectiveness-implementation pragmatic RCT. The allocation ratio is 1:1 for the intervention and control arms. The hybrid design places equal emphasis on simultaneously assessing implementation and effectiveness (23). Including key implementation-related outcomes (e.g., uptake, contextual implementation determinants, and adaptations) is consistent with recommendations for developing and evaluating complex interventions; early consideration of implementation increases the potential to extract more effective implementation strategies, rapid translational gains, and contextually relevant information for decision-makers (24). The trial is likely to produce results similar to those expected in practice as a pragmatic design was chosen to more closely replicate real-world conditions. Design features, such as eligibility criteria, recruitment, and flexibility of delivery and adherence, were selected to best align with practice (25). The following pragmatic features were included in the EMBOLDEN trial design:

i) recruiting a sample with broad inclusion criteria reflective of the general population of community-dwelling older adults;ii) conducting the study in existing community settings (e.g., community centers, recreation facilities);iii) leveraging existing resources, staff, and service delivery organizations in the intervention arm that are currently available in the real world setting;iv) supporting flexible delivery of the intervention (e.g., tailoring group-based strategies to participant group needs/interests/abilities and person-centerd tailoring of individual component), as would be done through other community programs in usual care;v) allowing flexibility in adhering to the intervention in ways that are consistent with usual care;vi) selecting primary and secondary outcomes that are participant-relevant (e.g., based on knowledge user input); andvii) using intention to treat analyses based on all available data.

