### Research questions

1.4

The study is designed to answer several primary and secondary research questions. The primary research questions to be addressed are:

1 Effectiveness: Does the 3-month EMBOLDEN intervention plus usual care increase moderate to vigorous physical activity (MVPA) compared to usual care alone in community-dwelling older adults residing in areas of high health inequity?2 Implementation: How is the EMBOLDEN intervention implemented and adapted across diverse urban neighborhoods?

The secondary research questions are:

1 Effectiveness:

i What is the effect at 3 months and 6 months of the EMBOLDEN intervention plus usual care compared to usual care on other outcomes (i.e., other smartwatch-derived measures of physical activity such as steps and distance traveled, self-reported physical activity, life-space mobility, nutritional risk, food security, health services utilization, health-related quality of life, resilience, loneliness, sense of community belonging, and collective efficacy) in community-dwelling older adults residing in areas of high health inequity?ii If a significant treatment effect is observed for the primary outcome (MVPA), which subgroups of older adults benefit the most from the intervention?

2 Implementation:

i What is the adoption rate of the EMBOLDEN intervention (i.e., the proportion of participants enrolled in the study who attend at least one group session and receive at least one system navigation support session)?ii What intervention dose is received by participants (i.e., number of group sessions and individual support sessions attended)?iii Regarding recruitment:

a What is the recruitment rate for the trial, and how does the sample compare to the target population?b What strategies contribute to the successful reach of older adults living in areas with health inequities?

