#### Sample size

2.1.7

The results of the pilot study suggested a sample size of 250–500 for this trial (all sites) (33). The sample size calculation was based on the effect size for the primary outcome measure (MVPA) and appropriateness for the statistical model used to analyze the trial data (62). The following two-pronged approach was used to acknowledge the uncertainty in the pilot trial estimate of effect: (1) eliciting MVPA effect sizes from other relevant published studies, and (2) calculating the sample size for various plausible values of key parameters in the calculation using values from the pilot augmented by estimates from other published studies (63). A literature review identified two recent systematic reviews for interventions promoting physical activity: Wright et al. (64) and Larsen et al. (65). The review by Wright et al. (64) was most useful because of their comprehensive reach (included 2,762 trials), use of MVPA variance estimates based on survey data from 5 cycles (2007–2017) of the Canadian Health Measures Survey (*n* = 13,173 respondents age 18–79) (66); and breakdown of MVPA effect sizes by distributional anchors (e.g., 25th/50th/75th percentiles), different populations (e.g., older adults), and follow-up periods (e.g., 3+/6+/12+ months).

The following parameters were fixed in all sample size calculations: *α* = 0.05, two-sided hypotheses, power = 0.80, and attrition (90% retention at 3 months and 80% at 6 months as per pilot results). The *total* sample size ranged from 190 to 1,074, depending primarily on the assumptions regarding effect size and variance. Despite this wide range, the positive qualitative feedback from intervention participants suggested that the higher effect size seen in the pilot may be realized, thus leading to the final estimated range for the sample size of 250–500 (~50 per site).

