Sensitivity analysis	Primary and secondary outcomes	Results from pooled analysis of multiple-imputed data sets will be consistent with original primary and secondary analyses	Explores impact of missing data using multiple imputation by chained equations (MICE), predictive mean matching, imputation by treatment group; employs modeling approach used in main analyses (i.e., LMM/GLMM, REML, LSM & 95% CIs)
Subgroup analysis	Moderate-Vigorous Physical Activity (MVPA) by sex category (male, female, other)	Treatment effect will be consistent across sex categories	Performed if overall treatment effect observed; employs modeling approach used in main analyses (i.e., LMM/GLMM, REML, LSM & 95% CI); separate models run for each category, interactions test (treatment group × sex) provided
	Moderate-Vigorous Physical Activity (MVPA) by 10-year age categories	Treatment effect will be consistent across age categories	Performed if overall treatment effect observed; employs modeling approach used in main analysis (i.e., LMM, REML, LSM & 95% CI); separate models run for each category, interactions test (treatment group × age) provided

a I = Intervention Group, C = Control Group.

b LMM = linear mixed model, GLMM = generalized linear mixed model, REML = restricted maximum likelihood estimation, LSM = least squares means (=model predicted means), CI = confidence interval.

c LMM/GLMM models will include the following fixed effects: outcome value at baseline, time (categorical), treatment group (categorical), and treatment × time interaction (categorical). Random effects for participants and sites will include either random intercepts, or the more complex model (random intercepts and random slopes) if suggested by spaghetti plots and fit statistics.

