A sensitivity analysis will be performed to further explore the impact of missing data. Multiple imputation will be employed with an imputation model that includes ancillary variables thought to be predictive of the probability of missingness and/or predictive of the responses. Multiple imputation by chained equations (MICE) will be conducted, with predictive mean matching used to avoid invalid values and ensure robustness regarding the misspecification of the imputation model (78). Although the analysis model will be simpler than the imputation model, this incompatibility is not a major concern (72). The number of imputations will be determined using the rule of thumb based on the percentage of participants with missing data (e.g., 70 imputed data sets if 70% of participants had any missing data) (79). The statistical model used in the primary analysis (LLM/GLMM) will be applied to the multiple data sets, and the results will be pooled using Rubin’s rules (80). For greater robustness, we will adopt the recommendation to conduct the multiple imputation separately by randomized group (81).

If a significant treatment effect is observed for the primary outcome (MVPA), a subgroup analysis for the primary outcome will be conducted in accordance with the following three rules: (1) the analyses should be regarded as secondary and exploratory, (2) the number of subgroups should be restricted to a select few, and (3) the subgroups should be specified *a priori* (82). The subgroups analysis will involve the following categorical variables: sex/gender (male/female/other) and age (10 year age categories). Subgroup analyses will also be performed on the imputed datasets, with imputations done separately by a randomized group as recommended (81).

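### The exploratory treatment × age test for MVPA cuts known exact age into 10-year categories, which costs power against a roughly linear age gradient; a single continuous-age interaction would recover it at almost no cost

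*Protocol article*

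**What the plan says.** Secondary effectiveness question (ii) in Section 1.4 asks, if the primary outcome shows a significant effect, "which subgroups of older adults benefit the most from the intervention". Section 2.3.3.2 answers it with two moderators: "The subgroups analysis will involve the following categorical variables: sex/gender (male/female/other) and age (10 year age categories"). The age row of Table 4 states the hypothesis "Treatment effect will be consistent across age categories" and the method "separate models run for each category, interactions test (treatment group × age) provided".

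The same section treats these analyses as secondary and exploratory, limits them to a few subgroups named in advance, and makes them conditional on a significant MVPA result. Eligibility (Section 2.1.2) is age 55 and older with no upper limit. The primary outcome definition (Section 2.1.5.1.1) uses age in years, as 207 − 0.7 × age, so exact age is in the data set. The article gives no band cut-points, number of bands, reason for banding, or power for any interaction test.

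**The concern.** Banding is a method that the article fixes explicitly, so it is not a detail left open for an analysis plan. If the MVPA effect rises or falls with age, a test across k unordered bands spends k − 1 degrees of freedom and discards the age variation inside each band. A test of one slope on continuous age uses all of that variation on one degree of freedom.

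At stake is the answer to the question of who benefits most. Age is one of only two moderators planned for it, and the stated expectation is that the effect does not vary. Lower power makes a result that appears to agree with that expectation more likely when a gradient exists. Separate models per band raise a different and smaller matter: a sparsely filled top band, analysed alone with site random effects, would give an unstable estimate.

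**Working it through.** **Inputs from the article.** Section 2.1.7 works at a 5% significance level with "two-sided hypotheses, power = 0.80, and attrition (90% retention at 3 months and 80% at 6 months as per pilot results" as its other fixed values. Over the scenarios tried there, the calculated "sample size ranged from 190 to 1,074, depending primarily on the assumptions regarding effect size and variance" and the article then settles on 250–500 overall, about 50 at each site. Section 1.3 gives the allocation: "The allocation ratio is 1:1 for the intervention and control arms". At 80% retention, 250–500 enrolled gives 200–400 with 6-month data.

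**The article's own figure.** The sample size is for the main effect, and neither effect size nor SD is stated, so it can only be solved backwards. With d = 2 × (1.96 + 0.84)/√(0.8N), the implied standardised main effect is 0.45 for N = 190, 0.40 for 250, 0.28 for 500 and 0.19 for 1,074. No interaction power is stated that could be reproduced.

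**Assumptions.** A linear gradient of g outcome SDs per 10 years of age, one outcome value per participant, and an age SD of about 8.07 years. Two band sets are used: 55–64, 65–74, 75+ (three bands, keeping about 82.4% of the age variance) and 55–64, 65–74, 75–84, 85+ (four bands, keeping about 88.1%). None of this is in the article.

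**Formulas.** Continuous age, 1 df: λ = N × 0.25 × (g × SD_age/10)². Bands, k − 1 df: the same λ multiplied by the share of age variance kept. Power is from the noncentral chi-square or F distribution at two-sided 0.05.

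**Step 1: loss by power of the continuous test.** This conversion depends only on the share kept and the degrees of freedom, not on N.

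| Continuous age | λ | Three bands (2 df) | Four bands (3 df) | Loss in points |
|---|---|---|---|---|
| 15% | 0.84 | 11% | 10% | 4–5 |
| 30% | 2.06 | 20% | 18% | 10–12 |
| 50% | 3.84 | 34% | 31% | 16–19 |
| 80% | 7.85 | 62% | 58% | 18–22 |
| 95% | 12.99 | 84% | 82% | 11–13 |
| 99% | 18.37 | 95% | 94% | 4–5 |

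The loss peaks near 70% continuous power. There, four bands that keep 85% of the variance leave 46%, a loss of 24 points. Across other plausible age distributions the range for 30% to 95% continuous power is about 10 to 24 points.

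**Step 2: scaled to this trial.** Take N = 400 analysed and d = 0.28, with a gradient per decade equal to the main effect, so g = 0.28. Then λ = 400 × 0.25 × (0.28 × 0.807)² = 5.11. Four bands: 0.881 × 5.11 = 4.50. Three bands: 0.824 × 5.11 = 4.21.

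| Gradient per decade, as a multiple of the main effect | Continuous | Three bands | Four bands |
|---|---|---|---|
| 0.25 | 9% | 7% | 7% |
| 0.5 | 20% | 14% | 12% |
| 0.75 | 39% | 26% | 23% |
| 1 | 62% | 43% | 40% |
| 1.25 | 80% | 62% | 59% |
| 1.5 | 92% | 79% | 76% |
| 2 | 99.5% | 96% | 96% |

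N = 200 with its own implied effect of 0.396 gives the same pattern to within a point.

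**Step 3: simulation check.** Ordinary least squares, four bands, 2,000 runs per setting. N = 400 and g = 0.3: 66% continuous against 43% banded (formula 68% and 45%). N = 200 and g = 0.5: 80% against 58% (formula 81% and 59%). The formula is confirmed to within about 2 points.

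**Step 4: sparse top band.** If ages are truncated normal on 55–95 with mean 68–74 and SD 8–9 before truncation, an 85+ band would hold about 3–8% of participants. That is roughly 8–20 of 250 or 15–41 of 500 before attrition, over two arms and ten sites.

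**The case against.** The strongest defence is that the size of the loss is not a property of this trial. It depends on an age distribution, a band count and a gradient that the article does not give, and the comparison favours the alternative by assuming a straight line. The gradients with the largest losses are steep: at one main effect per decade, the effect is zero ten years to one side of the mean age and doubled ten years to the other. A linear term would do worse on a plateau or a U-shape, and a spline check gives back part of the gain. Bands also answer a question about subgroups in a form that community partners can read. All of this stands, and it makes the figures conditional and the point a modest one. It does not remove the loss where a gradient is roughly linear and of middling size.

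Three stronger readings are tempting, and the article does not support them:

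- A reader might infer that a real gradient would usually be reported as consistency. No passage says that a non-significant interaction will be read that way; the consistency statement is a hypothesis, not a decision rule, and estimates come with 95% confidence intervals. On the figures above, four bands detect a gradient of 1.25 main effects per decade 59% of the time. At half a main effect per decade the continuous test also misses it about 80% of the time, so sample size is the main cause there.
- A reader might blame the separate models for the lost power. The same table cell also provides an interaction test, so the formal comparison does not rest on the separate fits.
- A reader might take four or more bands as fixed. No cut-points are given, and three bands with an open top at 75+ would be an ordinary choice. It would remove the very sparse 85+ cell but still lose 10 to 20 points or so over most of the range.

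**Conclusion.** The point holds as a low-cost improvement to an exploratory analysis. The article tests treatment × age on 10-year categories although exact age is available. If the gradient is roughly linear and there are three or four bands, this gives up about 10 to 24 points of power wherever the continuous test would have 30% to 95%, and only a few points for very small or very large gradients. The cause is the multi-degree-of-freedom categorical interaction test. The consequence is confined to secondary effectiveness question (ii): the analysis is conditional on a significant primary result, and the primary estimate, its test and the sample size are not affected.

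**What to change.** In Section 2.3.3.2 and the age row of Table 4, make the test of effect modification by age a single model on all participants: the primary mixed model plus centred continuous age and treatment × age at each follow-up. Report the interaction slope with its 95% confidence interval and, for readability, model-based treatment effects at a few ages such as 60, 70 and 80. Optionally add a quadratic or restricted cubic spline term as a check for non-linearity. Keep the 10-year bands for descriptive display, take their estimates from one interaction model instead of separate fits, and merge sparse top bands.

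The cost is a wording change before unblinding, with no new data and no more participants. One continuous-age interaction still meets the article's own rules that subgroup analyses be few, named in advance and exploratory. The downside is that a linear term has less power for a non-monotone age pattern, which the non-linearity check and the displayed bands address.

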A sensitivity analysis will be performed to further explore the impact of missing data. Multiple imputation will be employed with an imputation model that includes ancillary variables thought to be predictive of the probability of missingness and/or predictive of the responses. Multiple imputation by chained equations (MICE) will be conducted, with predictive mean matching used to avoid invalid values and ensure robustness regarding the misspecification of the imputation model (78). Although the analysis model will be simpler than the imputation model, this incompatibility is not a major concern (72). The number of imputations will be determined using the rule of thumb based on the percentage of participants with missing data (e.g., 70 imputed data sets if 70% of participants had any missing data) (79). The statistical model used in the primary analysis (LLM/GLMM) will be applied to the multiple data sets, and the results will be pooled using Rubin’s rules (80). For greater robustness, we will adopt the recommendation to conduct the multiple imputation separately by randomized group (81).

If a significant treatment effect is observed for the primary outcome (MVPA), a subgroup analysis for the primary outcome will be conducted in accordance with the following three rules: (1) the analyses should be regarded as secondary and exploratory, (2) the number of subgroups should be restricted to a select few, and (3) the subgroups should be specified *a priori* (82). The subgroups analysis will involve the following categorical variables: sex/gender (male/female/other) and age (10 year age categories). Subgroup analyses will also be performed on the imputed datasets, with imputations done separately by a randomized group as recommended (81).

##### Qualitative data analysis

2.3.3.3

Qualitative descriptive methodology (83, 84) will guide the exploration of participant experiences, and a hybrid conventional (inductive) and directed (deductive) content analysis approach will be used in analyzing the data (85). Data collection and analysis will be iterative; issues arising in early interviews will be explored further in subsequent interviews. Transcripts and meeting notes will be analyzed independently by two research team members using NVivo software (Lumivero) with a constant comparative method in which new information is compared to previous information (86). The initial coding tree will be reviewed with the broader qualitative team to establish broader categories and ensure consistent approaches across coders. Any coding discrepancies will be resolved by discussion. The data will be interpreted with input from the SGC.

##### Implementation evaluation

2.3.3.4

The implementation evaluation is designed as a mixed-methods formative evaluation to allow for iterative refinement of implementation strategies and to inform future scale-up and scale-out. Implementation evaluation will be guided by the RE-AIM framework (60). Table 1 provides the outcomes to be measured corresponding to each of the RE-AIM items. We will use quantitative data to examine implementation outcomes and qualitative data to explore the process of implementation.

The primary implementation outcomes will be analyzed using descriptive statistics expressed as percent/rate and corresponding 95% confidence intervals.

The process of implementation will be evaluated by examining qualitative data from several sources (committee documents/notes and meetings with interventionists, interventionist interviews, participant experience surveys, semi-structured interviews with SGC members reflecting diverse roles, focus groups with CAB members, and data sources both during and after the intervention. The data will be coded and analyzed using NVivo software, using the updated Consolidated Framework of Implementation Research (CFIR) (87) as a preliminary coding tree; codes will be revised using inductive analysis to identify data that do not align with the CFIR framework or to elucidate nuances within the CFIR domains and constructs. We will explore implementation determinants from the perspective of participants and interventionists. NVivo matrix queries will be used to explore differences in implementation determinants by perspective and site.

##### Community and citizen engagement evaluation

2.3.3.5

The community and citizen engagement strategy embedded throughout the EMBOLDEN research program, inclusive of this trial, will be evaluated annually by members of the SGC using the Patient-Centered Outcomes Research Institute’s Ways of Engaging-Engagement Activity (WE-ENACT) and Engagement Activity Inventory (NET-ENACT) Tools (88, 89).

##### Social network analysis (intervention participants only)

2.3.3.6

Network characteristics data will be extracted from the system navigation intervention tool, Genie®, at up to three timepoints depending on the uptake of this intervention component. We will construct network measures such as: (1) size of network (number of network members on the diagram), (2) diversity of network (number of types of relationships on the diagram, e.g., close family, distant family, acquaintances, friends = 4; close family = 1), (3) number of weak ties A (not family or friends; e.g., acquaintances, neighbors, colleagues), (4) number of weak ties B (number of network members in the outer circle of the diagram), (5) number of hobby or community groups, (6) frequency of contact (a sum, based on the frequency of contact with all network members, 4 = every day, 3 = at least once a week, 2 = at least once a month, 1 = less often), (7) number of women in the network, (8) number of pets. These will be used to develop measures of network change from Genie® visit 1 to Genie® visits 2 and 3 (as available). The questions we will explore in the network analysis include:

What is the network structure of older adults with health inequalities?What are the differences in network structure and network change for older adults living with or without a partner and of different socio-economic status?What are the predictors of positive network change for older adults with health inequalities?Is there an association between network structure and the support, health and well-being of older adults with health inequalities (e.g., change in physical activity; loneliness, health-related quality of life, social support)?

Genie® network data will be entered into statistical software using de-identified data by a member of the EMBOLDEN team. The network data for each participant will then be added to data collected in the intervention arm of the trial and only the anonymized data will be analyzed to answer the above questions. All data will be analyzed descriptively.

